### 6.2.3 Post-Intervention Assessment

At the completion of the 12 week exercise program, all participants will undergo a post-intervention assessment. The assessment will include all measures from the baseline assessment (LLFDI, 6MWT, gait speed, Gait Efficacy Scale, walking under challenging conditions (challenging gait tasks and figure of 8 walk), gait variability, SPPB, DSST, PHQ-9. Post-intervention testing will be completed at the sites (ILFs and senior housing sites) by research personnel masked to the intervention group and trained in the testing procedures.

In addition, we will also assess participant satisfaction. Participant satisfaction will be assessed using in-depth interviews and a satisfaction survey. In-depth phone interviews will be used to assess satisfaction in a subsample of participants (approximately 20%). We will randomly select a diverse sample of older adults representing the different intervention arms (On the Move, Standard, exercise leader, activity staff personnel) and the different sites (ILF and senior housing). We selected in-depth interviews instead of focus groups because we are more likely to draw people out, they are less intimidated, and more likely to be truthful. The interview will be developed by The Evaluation Institute under the direction of [name] (Co-Investigator) and with input from the other investigators and stakeholders (Community Advisory Board). The interview will include a mixture of closed and open-ended questions. Sample topics to be included in the interviews include perceived benefits and risks, satisfaction with the program, facilities, and instructor, and amount of individualized instruction. The interview will be pilot tested and modified accordingly prior to administration in the study. Pilot testing will ensure that the questions are understandable to our target population and that we are obtaining the information and feedback that we hope to obtain.

Satisfaction will also be assessed by surveys in all participants at the conclusion of the exercise program. The satisfaction survey includes five items measured on a Likert scale and three yes/no questions. The Likert items will assess degree of satisfaction with various components of the exercise program (i.e. the exercises, instructor, music, space, and the overall program). We will also use a series of yes/no questions to determine if the program has meet the participants' expectations, if they feel they have benefited from the program, and if they would recommend the program to others.

## **7 SAFETY ASSESSMENTS**

### **7.1 Expected Adverse Experiences**

1. Major risks such as a cardiac event or a fall are expected to be rare – expected to occur in less than 1% of people (less than 1 out of 100 people).(55) Gardner et al, 2000,(55) reviewed controlled clinical trials of exercise interventions for older adults at-risk for falling. No cardiac events or falls were reported in the 12 clinical trials reviewed. The at-risk older adults in the studies reviewed have slightly poorer physical performance than the older persons we expect to recruit for our study. In our recent MOBILE study, a 1 year cohort study of 120 older adults participating in 3 clinic visits over a 1 year period there were no cardiac events or falls reported. In all conditions of testing in which the

participant is standing and/or walking (eg conditions with a potential risk for falling), the participant will be directly supervised by the trained tester. The trained tester is present for all testing sessions. We expect this level of supervision reduces the risk of falling to an even greater degree.

2. Less severe risks of participation such as muscle soreness, fatigue, or minor sprains or strains with each assessment, are expected to be infrequent – expected to occur in 1-10% of people (1-10 out of 100 people). Gardner et al, 2000,(55) reviewed controlled clinical trials of exercise interventions for older adults at-risk for falling, finding reports of such side effects of the intervention reported in only 4 of the 12 studies reviewed. The side effects were not a reason for dropout from the study and were described as soreness or musculoskeletal symptoms, but no injuries.
3. There is a rare risk that confidentiality could be breached. All of the research records will be kept in a locked file cabinet and/or password protected files. All of the investigators and staff that assist with the management of the files are trained in the privacy and confidentiality regulations that govern research.

## **7.2 Minimizing Risk during Assessments and Interventions.**

All assessments approved in this study are considered to be a part of everyday clinical practice. We have minimized risks we believe by applying usual safeguards for the assessment of gait. Assessment side effects, such as muscle soreness, fatigue, or minor sprains or strains with each assessment, will be recorded by the physical therapist and monitored by [name], the Principal Investigators in consultation with the physician investigator, [name]. Based upon the existing literature and our own clinical experience, we anticipate the frequency of these side effects to be extremely low.(55)

We will maximize the safety of our subjects with the following procedures.

1. Individuals with absolute contraindications to testing will be excluded based on the inclusion/exclusion criteria.
2. Testing will be carefully monitored by trained testers and will be adjusted according to the American College of Sports Medicine Guidelines for Exercise Testing and Prescription.(34)
3. In all conditions of testing in which the participant is standing and/or walking (eg conditions with a potential risk for falling), the participant will be directly supervised by the trained tester.

## **7.3 Confidentiality.**

Participant's confidentiality will be protected in the data collection process. All personnel involved with the research have read and signed a Confidentiality statement, and approval is being obtained from the University of Pittsburgh Biomedical Institutional Review Board. Consent forms and data collection forms that identify the participant by name will be stored in a locked cabinet. All computers are password protected. If the data are used in scholarly presentations or journal articles, the investigators will protect the anonymity of individual

participants and will report only aggregate data (eg group means) where appropriate. The Principal Investigator will review data confidentiality processes monthly or as indicated with the project staff. The Investigators are all certified in Research Practice Fundamentals, Human Subjects Research Module.

#### **7.4 Participant Education about Potential Risks**

Potential risks associated with study-related activities and interventions will be explained to each participant by trained study personnel during the informed consent process. Each participant will be instructed to report the occurrence of an AE to appropriate study staff at scheduled data collection times, to PTs administering the intervention, or spontaneously at any other time. Participants also will be encouraged to report concerns about the safety of participating in the study to any research staff.

#### **7.5 Adverse Events and Serious Adverse Events**

If an adverse event occurs during testing or intervention, staff or activity personnel will assess the situation and provide immediate assistance to the participant if necessary. If a medical emergency should occur, staff will immediately contact 911. They will describe the incident to the 911 operator and provide their location. They will also contact the facility director to make them aware of the situation. In each testing/exercise space, we will post a copy of the emergency plan which will include the number to call (911) and the address of the facility. All staff will be informed of the emergency procedures prior to starting the interventions and they will be reviewed every 6 months. Once the emergency situation is under control, the staff will contact the study PI to notify them of the situation. The PI will report unexpected or adverse events in accordance with the University of Pittsburgh IRB guidelines. As a group the PI and Co-Is review the adverse events to determine if they are expected vs unexpected and serious vs not serious. All events are reported to the irb who will also review the events. The study coordinator ([name]), study biostatistician ([name]) and study physician ([name]) who are unblinded will track the events to determine if there are an unequal number of events between the groups.

A clinical complication form will be completed any time an incident (accident, injury, illness, problems with medication, etc.) occurs or a subject reports an episode. Complications will be categorized as study related, possibly study related, or not study related. Any complications that are categorized as either study related or possibly study related will be reported to the IRB per protocol if the event is an unexpected event, and/or is of serious or moderate to severe in nature as defined by the IRB. A separate clinical complication form will be completed for each incident that may occur in each subject. The form will be kept in the subject's research record.

### 7.5.1 Classifying Adverse Events (AE)

An AE is any unfavorable or unintended medical occurrence in a human study participant that has taken place during the course of a research project, including any abnormal sign, symptom, or disease, whether or not related to participation in the research.

For the purposes of this study, any event that meets the criteria for a severe adverse event (SAE), is unexpected, or results in injury to the participant while he/she is under the supervision of study related personnel will be classified as a reportable adverse event (RAE). Adequate review, assessment, and monitoring of RAEs require they be classified as to severity, expectedness, and potential relatedness to the study intervention.

### 7.5.2 Severity

The following guidelines will be used to determine level of severity:

Mild: Awareness of signs and symptoms, but easily tolerated and causing no loss of time from normal activities. No specific medical attention is required.

Moderate: Discomfort enough to cause a low level of inconvenience or concern to the participant and may interfere with daily activities. Symptoms may require minimal, local or noninvasive medical intervention.

Severe: Events interrupt the participant's normal daily activities and are usually incapacitating. Significant symptoms may require hospitalization or invasive medical intervention.

Life-threatening/Disabling: Events that may involve acute, life-threatening metabolic or cardiovascular complications (such as circulatory failure, hemorrhage, sepsis) or life – threatening physiological consequences. Intensive care or emergent invasive procedure is required.

Death: Causing death.

Severity is not synonymous with seriousness. A severe headache is not necessarily an RAE. However, mild chest pain may result in a day's hospitalization and thus would be classified as a RAE.

### 7.5.3 Expectedness

AEs will be assigned as to whether they were expected or unexpected based on current knowledge. Categories are defined as follows:

Expected: An AE that is anticipated on the basis of prior experience with the intervention under investigation; an event that can be attributed to the underlying condition of the participant being studied; or an event that can be attributed to the patient population being studied (see section--- Expected AEs). Expected AEs are captured in a standardized way by study personnel.

Unexpected: An AE that was not anticipated on the basis of prior experience with the underlying intervention under investigation; an event that can be attributed to the underlying condition of the participant being studied; or to the patient population being studied or an expected event whose frequency or severity exceeds what is anticipated. Unexpected events are reportable.

#### 7.5.4 Relatedness

The PI in consultation with the Co-Investigators and an independent safety monitor will determine the degree to which RAEs are related to study procedures using the criteria below.

Definitely related: The adverse event is clearly related to the investigational procedure – i.e., an event that follows a reasonable temporal sequence from administration of the study intervention, follows a known or expected pattern of response to the study intervention, that is confirmed by improvement on stopping and reappearance of the event on repeated exposure, and that could not be reasonably explained by the known characteristics of the participant's clinical state.

Possibly related: An adverse event that follows a reasonable temporal sequence from administration of the study intervention of that follows a known or expected pattern of response to the study intervention, but that could readily have been produced by a number of other factors.

Unrelated: The adverse event is clearly not related to the investigational procedure (i.e. another cause of the event is most plausible; and/or a clinically plausible temporal sequence is inconsistent with the onset of the event and the study intervention and/or a causal relationship is considered biologically implausible).

### 7.6 Expected AEs

Expected adverse events (AEs) will be captured through interviews at 12, 24 and 36 weeks, based on the Health Status Update questionnaire. The following are expected adverse events that have been listed in the informed consent form:

- Muscle soreness
- Fatigue
- Chest pain
- Breathing problems
- Cardiac event
- Fall (with or without injury)

### 7.7 Reportable AEs (RAEs)

Reportable AEs are events that have potential implications for participant safety and that require individual reporting. RAEs will be defined as events that fall into at least one of the following categories:

1. Serious adverse event (SAEs) - SAEs will be defined as any adverse event that results in death, is life threatening, or places the participant at immediate risk of death from the event as it occurred, requires or prolongs hospitalization, causes persistent or significant

disability or incapacity, results in congenital abnormalities or birth defects, or is another condition which investigators judge to represent significant hazards.

2. Unexpected AEs - An unexpected AE is defined as medical events that occur during study participation, but do not commonly occur in the study population and which are not listed in the informed consent document or study protocol.

3. AEs related or possibly related to the research intervention – defined as any AE which in the opinion of the principal investigator, the incident, experience or outcome more likely than not was caused by the procedures involved in the research.

Events that cannot be clearly defined as “reportable” will be discussed with the study physician and the PI to determine if they should be reported. All reportable events will be captured on an Adverse Event form which will be filed in the participant binder and then reported using the following guidelines.

## **7.8 Reporting of Events**

The study PI has primary responsibility for the safety of participants as it relates to the study protocol. The study coordinator will be responsible for reviewing adverse events and assuring accurate and timely reporting of the adverse events. The co-investigators (including study physician) will review, evaluate and classify adverse events and provide follow-up for events until they are resolved. The PI will be responsible for reporting study-defined AEs and SAEs to the University of Pittsburgh institutional review board (IRB) according to their timeline and format.

## **8 INTERVENTION DISCONTINUATION**

### **8.1 Interruption to Exercise Participation**

Attendance will be taken at all exercise session and will be documented on the attendance sheet. Participants who miss three consecutive classes will be contacted by phone to determine the reason for the absences. Participants who miss three or more consecutive classes due to illness or injury will be required to obtain medical clearance from their physician prior to returning to the exercise class. Participants who miss three consecutive classes for other reasons (vacation, ill spouse, caregiving responsibilities, transportation etc.) will be encouraged to attend as many classes as possible.

### **8.2 Intervention Discontinuation**

At any time, the study team may recommend discontinuation of any component of the intervention or intervention group of the study for any of the following reasons:

1. Compelling evidence from this or any other study of an adverse effect of the study intervention(s) that is sufficient to override the potential benefit of the interventions to the target population
2. Compelling evidence from this or any other study of a significant beneficial effect of the study intervention(s), such that it is continued denial to other study group(s) would be unethical
3. A very low probability of addressing the study goals within a feasible timeframe.

The research team may decide at any time to remove a participant from the research study if the team feels the participant is unsafe to continue. Participation in the research study will be discontinued if a participant's walking ability worsens; for example, if a subject who has osteoarthritis of the knees exhibits a significant increase in pain that negatively affects their walking ability. Participants can be removed from the study if they have unstable vital signs as a response to exercise. A participant can also be removed from the study if any new medical condition, injury or illness is discovered during the course of treatment that would make the participant unsafe to continue.

The research team may decide at any time to discontinue training of a staff activity person if the teams feels the staff activity person is unsafe to continue. If training of a staff activity person is discontinued, an exercise leader will take over as instructor for the exercise class to keep our obligation of the exercise class to the community. If such a change becomes necessary after the class has begun, we will exclude that particular class from all analyses. If such a change becomes apparent before the class begins, and the entire class is taught by an exercise leader, we will include the class in Aim 1 analysis.

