### 5.6 Adherence Assessment

A roster of participants will be developed for each group exercise class. At the beginning of each class, attendance will be recorded by the exercise leader or staff activity personnel. Reasons for missed classes will be recorded when available. Attendance rate ([number of sessions attended

544 by the participant/total number of classes offered, i.e 24] X100%) will be calculated for each  
545 participant and will be the main indicator of adherence.

546

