### 8.3 Voluntary Participation

The participants' participation in this research study is completely voluntary. The participant may withdraw, at any time, their consent for participation in this research study. Any identifiable research information recorded for, or resulting from, their participation in this research study prior to the date that they formally withdrew their consent may continue to be used and disclosed by the investigators. To formally withdraw consent for participation in this research study the participant should provide a written and dated notice of this decision to the principal investigator of this research study. If the participant withdraws from the intervention, study staff will ask permission to continue to follow the participant for follow-up assessment. If participation is discontinued for medical reasons and the participant is unable to complete the performance-based testing, all attempts will be made to obtain the self-reported outcomes.

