## 9 STATISTICAL CONSIDERATIONS

### 9.1 General Design Issues

A randomized trial is needed to control for confounding factors that affect the outcome. There are no ethical issues regarding a randomized trial since both groups will be receiving an active exercise intervention delivered by trained personnel. We carefully considered the advantages and disadvantages of randomizing at the level of the facility and the resident. Given the amount of interaction that occurs between subjects within a facility, it is imperative that we conduct a cluster randomized trial, and randomize by facility to exercise programs. If we randomize at the resident, participants would discuss details of their intervention and cause cross-contamination between the intervention arms. Unlike a traditional trial in which participants are randomized as they are being recruited, a cluster randomized trial also affords the additional benefit of examining the facility characteristics such as type (independent living/senior high rise) and size, and ensuring a balance in those characteristics is achieved by design rather than chance. Once the facilities are randomized to exercise program, we will then randomize within facility for delivery mode (i.e. subjects will be randomized to either an exercise leader or staff activity person led exercise program). Randomization for delivery mode will occur after baseline testing. We will use a commercially available high quality pseudo-random deviate generator such as that available in SAS® (SAS Institute, Inc., Cary, North Carolina) known to be free of serial correlations(56) to randomize facilities to the two arms in a 1:1 ratio, stratified by facility type. In addition, the proposed design reaps the advantages of a paired comparison for the exploratory hypothesis (Aim 2) as both exercise leaders and staff activity personnel will be delivering On the Move in the same set of facilities, where feasible to train a staff person ready to lead the class safely and per protocol.

The main outcomes are self-reported function and disability (Late Life Function and Disability Index/LLFDI) and walking ability (6-minute walk test/6MWT and gait speed). We will also examine satisfaction, attendance rates and adverse event (falls, soft tissue injuries, muscle soreness, etc) rates.

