### 9.2 Sample Size

We base our sample size justification on prior data from our RESTORE and PRIME pilot studies, two-tailed tests conducted at the  $\alpha=0.05$  level, a conservative attrition rate of 10% between baseline and follow-up assessments, practical consideration of a class size of 10 participants for group exercise, computational techniques that match our study design and proposed analytical approach as much as possible within the constraints of already published methodologies and commercially available sample size and power software (PASS 2002®, Number Cruncher Statistical Systems, Inc., Kayesville, Utah), and ability to detect differences that correspond to published meaningful change criteria(57) or moderate Cohen's effect sizes of  $d=0.5$ .(58)

The numbers needed to enroll in order to detect statistical significance of intervention effect when delivered by an exercise leader (Aim 1), are presented in **Table 1**. We take into account the clustering of participants by facility by assuming an intracluster correlation of 0.1 and a resulting design effect of 1.90 to appropriately inflate the sample size accordingly.(59) In

summary, a total of 280 participants with 140 in each arm will allow us to detect statistical significance in intervention effects in all main outcomes with at least 80% statistical power.

**Table 1. Number needed to enroll for detecting effects of intervention incorporating clustered design (x1.90), attrition (10%), and rounded up to class size of 10.**

| Outcome                    | Prior Information                |                                 |                                         | Estimated Sample Size                                   |                                 |
|----------------------------|----------------------------------|---------------------------------|-----------------------------------------|---------------------------------------------------------|---------------------------------|
|                            | Baseline Standard Deviation (SD) | SD in Baseline-Follow up Change | Meaningful Difference Targeted (Source) | Completers Needed Per Arm assuming No Clustering | Number Needed to Enroll Per Arm |
| LLFDI Overall Function     | 6.15                             | 4.86                            | 3.08 ( $d=0.5$ )                        | 41                                                      | 90                              |

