### 9.3 Data Analyses

#### 9.3.1 Overview

All statistical analyses will be performed or overseen by [name] using SAS® version 9 (SAS Institute, Inc., Cary, North Carolina) and Salford Predictive Miner® (Salford Systems, Inc., San Diego, California) based on the **intention-to-treat** philosophy. We will begin by summarizing data by arm and time point as well as pre- to post-intervention change using appropriate descriptive statistics for continuous (mean, standard deviation, median, range) and categorical (frequencies, percentages) to elicit information about general data quality and their distributional characteristics. Next, we will perform the modeling and inferential analyses to address the main hypotheses. First, the baseline participant characteristics will be compared between the two arms (see Avoidance of Bias below). Although no significant differences are expected, any significant differences will be noted and accounted for as covariates in the main analyses. Second, main analyses to address Aims 1-3 will be performed as outlined below. If residuals reveal violations of linear models assumptions, we will Box-Cox transform(60) the response variables. The two-step protected test approach will be used to control the experimentwise type I error rate from multiple outcomes, and multiple imputation(61, 62) will be used to account for any missing data in the main analysis. Third, we will perform the exploratory analyses to address Aim 4, using a data mining philosophy. Finally, we will perform a set of exploratory analyses to potentially extend our findings and generate new hypotheses, as well as a set of sensitivity analyses to assess the robustness of our findings.

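### Section 8.2 ends study participation, not just the exercise class, when walking worsens; week-12 walking tests for those stopped are only implied

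*Supplement*

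**What the plan says.** The sentence in Section 8.2 reads "Participation in the research study will be discontinued if a participant's walking ability worsens". Its example is knee osteoarthritis with pain that has increased enough to affect walking. The neighbouring rules on removing individuals are discretionary; this one is mandatory, and it names the study rather than the class. Section 10.3.3 lists a change in health among the reasons for terminating study participation.

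Other text points towards follow-up:

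- Section 8.2 is headed as dealing with the intervention.
- Section 8.3 provides: "If participation is discontinued for medical reasons and the participant is unable to complete the performance-based testing", then "all attempts will be made to obtain the self-reported outcomes".
- Section 8.3 also has staff ask permission for continued follow-up, but only when the participant withdraws from the intervention.
- Section 6.2.3 says that "all participants will undergo a post-intervention assessment" when the 12-week program is complete. It does not mention people removed earlier.
- Section 9.3.1 bases the analysis on intention to treat, with multiple imputation that "will be used to account for any missing data" in the main analysis.

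Section 9.1 names the 6MWT and gait speed, with the LLFDI, as the main outcomes. Section 9.2 allows "a conservative attrition rate of 10" percent.

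**The concern.** The trigger for removal and two of the main outcomes concern the same thing: how well the participant walks. If site staff apply Section 8.2 as written, the people most likely to have a poor 6MWT or gait speed result have no result. Intention to treat depends on having those results. Imputation that assumes data are missing at random does not fully repair a loss that depends on the unseen value.

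The direction of any bias depends on how the rule falls on the two arms. A spurious difference needs unequal removal. That is possible, because On the Move has 40 of its 50 minutes standing, against 10 minutes (Section 3) or under 10 (Section 5.3) in the standard program. The LLFDI is less exposed, since Section 8.3 asks for self-report even when the walking tests cannot be done.

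**Working it through.** **1. The texts side by side.** Section 8.2 ends study participation when walking worsens. The Section 8.3 fallback to self-report applies to people medically discontinued who cannot do the performance tests. An exception of that kind presupposes that those who can do the tests are tested. Section 6.2.3 covers everyone who reaches the end of the program. So follow-up of a participant stopped by the team who can still walk is implied twice and stated nowhere, while the sentence ending study participation is explicit.

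**2. The plan's own figures.** Section 9.2, Table 1, for gait speed: change SD 0.20 m/s, target 0.10 m/s, 64 completers per arm, design effect 1.90, attrition 10%.

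- 64 × 1.90 / 0.90 = 135.1, rounded up to a multiple of 10 = 140 per arm. This reproduces, and nothing here changes it.
- Expected completers: 140 × 0.90 = 126 per arm, which allows for 14 losses.

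**3. Shift if removal occurs in one arm only.** These assumptions are not in the documents: change is normal; a fraction p of one arm is stopped and not tested; the latent reason for stopping correlates ρ = 0.5 with the week-12 change; there is no imputation.

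Shift in the mean change of those tested = ρ × SD × φ(z_p) / (1 − p)

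| p | Number of 140 | φ(z_p)/(1 − p) | Gait speed (SD 0.20) | 6MWT (SD 42.8) |
|---|---|---|---|---|
| 0.02 | about 3 | 0.0494 | 0.5 × 0.20 × 0.0494 = 0.0049 m/s | 1.1 m |
| 0.05 | 7 | 0.1086 | 0.5 × 0.20 × 0.1086 = 0.0109 m/s | 2.3 m |

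The targets are 0.10 m/s and 50 m. Both removal rates lie inside the 14 losses allowed.

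**4. Effect on the test.** SE of the difference = 0.20 × √(2 × 1.90/126) = 0.0347 m/s. A shift of 0.0109 is 0.0109/0.0347 = 0.31 SE, which moves a two-sided 5% error rate to about 6.1%. With 5% removed in one arm and 2% in the other, the net shift is 0.0109 − 0.0049 ≈ 0.006 m/s and the error rate about 5.3%. Equal removal gives no shift when there is no effect.

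**5. What imputation from baseline leaves.** The correlation of baseline with change is (SDf² − 0.13² − 0.20²) / (2 × 0.13 × 0.20), where SDf is the follow-up SD. Assuming SDf of 0.20 to 0.13 gives −0.33 to −0.77. In a simulation of 4 million draws, regression imputation on baseline within the arm reduces the 0.0109 shift to between 0.0097 and 0.0045 m/s.

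**6. The same rule in both arms when there is a true effect.** Assume that everyone whose change falls below −0.25 m/s is lost. A sharp cut of this kind overstates the size; it serves to show direction.

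- True mean gains 0.15 and 0.05: 2.3% and 6.7% lost; those tested average 0.161 and 0.078; the difference of 0.10 shows as 0.083.
- RESTORE gains 0.21 and 0.14: 1.1% and 2.6% lost; those tested average 0.216 and 0.152; the difference of 0.07 shows as 0.0635.

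Both results move towards zero.

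**The case against.** The strongest reply is that this is a safety stop in a section on stopping the intervention, and that the rest of the plan already treats testing as the default after a stop. Section 8.3 makes an exception only for those unable to be tested, Section 6.2.3 tests everyone, and the analysis is intention to treat. A reader might infer from Section 8.2 alone that the plan drops people who get worse. The documents do not support that. What stands against the reply is that these passages only imply follow-up, while Section 8.2 is explicit and mandatory and Section 10.3.3 agrees with its literal reading.

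A reader might also infer that removal acts like a cut on measured change. It cannot. The Section 6.1 schedule has no 6MWT or gait speed test between the start of a class and the week-12 test, so worsening is a staff judgement of pain or safety. That is why the illustration uses a correlation of 0.5. A perfect trigger would double the shift and is not realistic.

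Nor do the documents support the inference that the rule would manufacture a benefit for On the Move. That requires more removals in that arm, and no rates are given. RESTORE kept 47 of 50 participants (94%), so 5% removed for worsening walking in one arm alone would be high.

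Finally, the choice of variables for the imputation model is detail commonly left to a separate analysis plan, and none is shown. It is not part of this point.

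**Conclusion.** The point holds as a conflict of wording with a small likely consequence. Read literally, Section 8.2 makes 6MWT and gait speed missing because of the outcome, contrary to the intention-to-treat analysis. The passages that point the other way do so only by implication.

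The size is unknown. On the one-arm assumptions above it is about 0.005 to 0.011 m/s for gait speed, a tenth or less of the target, and about 1 to 2 m for the 6MWT. Imputation from baseline would reduce it somewhat. A common rule in both arms attenuates a true effect, and the LLFDI is largely protected. Low priority, but worth correcting because untested participants cannot be recovered afterwards.

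**What to change.** Keep the safety stop. Reword Section 8.2 so that worsening walking stops the exercise intervention only. State in Sections 8.2 and 8.3 that anyone stopped by the team stays in week-12 follow-up with consent: 6MWT and gait speed if safe, self-report otherwise.

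Optionally, add one delta-adjusted sensitivity analysis for walking outcomes missing after such a stop. A range of 0 to about −1 change SD is enough (gait speed 0 to −0.20 m/s, 6MWT 0 to about −43 m). At a correlation of 0.5 with 5% stopped, those lost average 0.5 × 0.20 × 0.1031/0.05 = 0.21 m/s below the arm mean, or about 1 SD.

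The cost is a short protocol wording change. The week-12 visit is already scheduled at the sites.
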